## Abstract

**Background:**

Type 2 diabetes (T2D) mellitus treatment as a chronic disease requires adequate adherence to treatment including controlling blood glucose levels and lifestyle management. The aim of this study is to investigate the factors affecting of adherence to T2D treatment from the perspective of patients and design an intervention program based on Pender’s health promotion model (HPM) to increase T2D treatment adherence in Bandar Abbas, a city located in the south of Iran.

**Methods:**

This mixed method study will consist of qualitative stage, questionnaire design and a randomized, open-label, parallel-group interventional study based on HPM in southern Iran. Sampling for qualitative stage will continue until reaching the saturation. In the intervention stage, participants will be 166 T2D patients referring to the Bandar Abbas Diabetes Clinic will be randomized into intervention and control groups (allocation 1:1). After identifying the factors affecting adherence to treatment in T2D patients by qualitative study and literature review, a questionnaire based on HPM will be designed. In the next stage, 10 sessions of intervention for the intervention group will be designed. To evaluate the effect of the intervention, intervention and control groups will be tested for hemoglobin A1c (HbA1c) before and 3 months after the intervention.

**Discussion:**

This designed study is a program for improving treatment adherence in T2D based on the HPM model and contributes to a better understanding of effective factors in adherence to treatment in T2D patients. The results of this project can be used for macro-diabetic planning.

**Trial registration:**

This study is registered on the Iranian Registry of Clinical Trials (IRCT20211228053558N1: https://www.irct.ir/trial/61741) and first release date of 17th March 2022.

**Supplementary Information:**

The online version contains supplementary material available at 10.1186/s13063-022-07027-9.

## Administrative information

Note: the numbers in curly brackets in this protocol refer to SPIRIT checklist item numbers. The order of the items has been modified to group similar items (see http://www.equator-network.org/reporting-guidelines/spirit-2013-statement-defining-standard-protocol-items-for-clinical-trials/).

## Introduction

### Background and rationale {6a}

Type 2 diabetes mellitus (T2D), one of the most common global chronic diseases, is a serious threat to the public health and healthcare systems [1]. According to the 10th edition of the IDF Diabetes Atlas, it was estimated that there are 536.6 million people with diabetes worldwide in 2021 and were expected to increase to 783.2 million by 2045 [2]. The prevalence of diabetes mellitus in Iran is 11.4% among 25–70 years [3], and expectation until 2030 is 9.24 million cases (6.73 million diagnosed and 2.50 million undiagnosed) [4].

Treatment of T2D as a chronic disease requires adequate adherence to treatment: controlling blood glucose levels, and lifestyle management, including medical nutrition therapy, physical activity, and psychosocial care [5]. Adherence is defined as “the extent to which a person’s behavior, taking medication, following a diet, and/or executing lifestyle changes, corresponds with agreed recommendations from a health care provider” [6].

A systematic review study reported that in several developed countries treatment adherence in diabetic patients varies from 38.5 to 93.1% [7]. Control of hyperglycemia in Iran, despite the availability of medications and insulin coverage, is not sufficient [8]. A cross-sectional study (2021) reported 52.75% adherence to T2D treatment in Iran [9]. Treatment non-adherence in diabetic patients is associated with subsequent complications, increased mortality, increased treatment costs, reduced quality of life and even increased economic burden [7].

Since adherence to treatment in T2D is a complex behavior [10], theoretical-based qualitative studies can help researchers to understand the reason for this complex behavior and design suitable interventions [11]. Previous studies showed that theory-based health-promotion interventions can play an effective role in promoting healthy behavior in the diabetic patients [12, 13]. One of these models is Pender’s health promotion model (HPM). This model focuses on the role of experience in shaping behavior for explaining healthy behavior. HPM enables health professionals to discover a process that encourages people to adopt health-promotion behaviors, such as treatment adherence [14]. It includes three factors, namely, individual characteristics and experiences (including personal factors and previous behaviors), behavior-specific cognitions and affect (including structures such as perceived benefits and barriers and perceived self-efficacy), and behavioral outcomes (health-promoting behavior is the desired behavioral outcome and is the endpoint in the health promotion model). Behavior-specific cognition and affect includes the perceived benefits of behavior, perceived barriers to behavior, perceived self-efficacy, activity-related affect, and interpersonal and situational influences. They can lead to adherence to health-promotion behaviors compared to immediate competing demands and preferences [15]. Therefore, investigating these constructs in order to evaluate their impact on T2D patients’ treatment adherence can be useful in guiding us towards an effective intervention for these patients.

Considering the increasing prevalence of diabetes in Iran [16], and evidence gap in T2D in different areas of Iran, there is a need for more research, especially in remote regions [17]. Unhealthy lifestyle including physical inactivity and unhealthy diet is common in southern Iran [18], and this can be effective in T2D patients’ treatment adherence in this region. Therefore, the aim of this study is to investigate the factors affecting of adherence to T2D treatment (medication, diet and physical activity) from the perspective of patients and design an intervention program based on HPM to increase T2D treatment adherence in Bandar Abbas, a city located in the south of Iran.

### Objectives {7}

The objective of this study will be to

Understand the factors affecting to T2D patients’ treatment adherence at different levels from the perspective of patientsDesign a valid and reliable instrument to measure T2D patients’ treatment adherence based on HPMDesign, implement, and evaluate intervention program to improve T2D patients’ treatment adherence based on HPM

### Trial design {8}

This mixed-method study consists of 3 phases.

Need assessment as the first step aims to identify the factors affecting adherence to treatment in T2D patients. Different qualitative and quantitative data sources will be used for need assessment. After combining the results of the need assessment, a questionnaire based on HPM to measure adherence to medication, physical activity, and diet will be designed. In the next stage, based on earlier phases the intervention will be designed. The intervention phase with a superiority design is a randomized, open-label, parallel-group study. The participants will be randomly assigned at a 1:1 ratio to control and intervention groups. The intervention group will participate in an intervention program to improve T2D treatment adherence treatment (medication, diet, and physical activity) based on the Pender health promotion model. To evaluate the effect of the intervention, intervention and control groups will be tested for hemoglobin A1c (HbA1c) before and after the intervention.

## Methods: participants, interventions, and outcomes

### Study setting {9}

To design this study, a research team consisting of three health education and promotion specialists, one doctor of internal medicine, and one biostatistics expert, is formed. The study population includes T2D patients referring to the Diabetes Clinic of Shahid Mohammadi Hospital in Bandar Abbas, and the place of study is the diabetes clinic of Shahid Mohammadi Hospital, the largest general hospital in Hormozgan province in the south of Iran. This clinic is the largest diabetes clinic in the province, where 1500 T2D patients have been registered. The study framework is summarized in Fig. 1.

**Fig. 1 Fig1:**
[figure not shown]
The study framework

### Eligibility criteria {10}

#### Qualitative stage

Eligible participants will be those who identify as women or men and are over the age of 80, have to be confirmed T2D, having rich and useful experiences of living with diabetes and their willingness to share their experiences with the researcher, and being able to participate in interviews and transfer information and experiences.

#### Intervention stage

Eligible participants will be women or men, over the age of 80, need to express their consent to participate in the research and have registered a medical case in the Diabetes Clinic of Shahid Mohammadi Hospital as a patient with T2D and also live in Bandar Abbas.

The exclusion criteria also include participating in intervention sessions (absence of more than two interventional sessions) and not referring to the Diabetes Clinic of Shahid Mohammadi Hospital.

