### Sample size {14}

#### Qualitative stage

Considering the fact that qualitative studies seek rich data and the greatest diversity, participants will not select solely from those who refer to the Diabetes Clinic of Shahid Mohammadi Hospital in Bandar Abbas (Bandar Abbas Diabetes Center). Sampling will be carried out using a maximum variation of the purposive sample (in terms of age, educational status, marital status, employment status, diabetes status, and adherence to treatment status). Sampling will continue without any limit on the number of samples until reaching the saturation stage. We will use the information from the medical files registered with the Diabetes Clinic of Shahid Mohammadi Hospital in Bandar Abbas to identify eligible patients

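### Both stages admit only patients over 80, with no reason given, which conflicts with the maximum-variation sampling plan and does not fit the stated aim and population

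*Protocol article*

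**What the plan says.** Eligibility criteria {10} sets the age rule twice.

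- Intervention stage: "Eligible participants will be women or men, over the age of 80". Participants must also be registered at the clinic as type 2 diabetes patients and "also live in Bandar Abbas".
- Qualitative stage: "Eligible participants will be those who identify as women or men and are over the age of 80".

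Neither place gives an upper limit or a rationale.

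Other sections describe the people to be studied differently.

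- Study setting {9}: "The study population includes T2D patients referring to the Diabetes Clinic of Shahid Mohammadi Hospital in Bandar Abbas". It describes the clinic as the province's largest, "where 1500 T2D patients have been registered". Age is not mentioned.
- Sample size {14}, Qualitative stage: purposive sampling for maximum variation "in terms of age, educational status, marital status, employment status, diabetes status, and adherence to treatment status".
- The Abstract, Background and rationale {6a} and Objectives {7} refer to type 2 diabetes patients, and the aim is placed in Bandar Abbas. None mentions an elderly group. The national prevalence cited in the background is for ages 25 to 70.
- Sample size {14}, Intervention stage: 76 per group, raised to 83 for drop-out, so 166 in total.

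**The concern.** An eligibility criterion defines the population to which the result applies. Here it selects the very old, while the rest of the article reads as a study of type 2 diabetes patients in general.

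If the rule is applied as printed, the interviews and the trial are all confined to people over 80. The result then does not answer the stated question about adherence among type 2 diabetes patients in Bandar Abbas. If the rule is not applied, every participant aged 80 or under falls outside the published criteria, and a reader cannot tell whom the trial was meant to enrol.

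There is also a recruitment question for the trial stage, because one clinic's register must supply all 166 participants.

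**Working it through.** **Consistency of the text**

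1. Age limit against sampling plan. The interview sample is to vary as widely as possible in age and employment status. A floor of 80 leaves only the top of the age range and can be expected to leave little variation in employment. This is the most direct conflict, and both statements concern the same stage.
2. Age limit against aim, objectives and setting. These are silent on age. Eligibility may narrow a source population, so this is an inconsistency and not a literal contradiction. Narrowing this severe would normally appear in the aim, and it does not.
3. Age limit against background. The cited prevalence covers ages 25 to 70, a range that contains nobody the rule would admit.

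**The plan's own sample size**

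Inputs from Sample size {14}: SD 29.7, difference 13.5, two-sided alpha 5%, power 80%. The standard two-mean formula, with z values 1.960 and 0.842 entered unsquared inside the bracket, gives

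n = 2 × (1.960 + 0.842)² × (29.7 / 13.5)² = 2 × 7.849 × 4.84 = 75.98, so 76 per group.

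This matches the stated 76. For drop-out, 76 × 1.10 = 83.6 and 76 / 0.90 = 84.4. The stated 83 is within two patients of either result, and the total is 2 × 83 = 166. Age does not enter the formula, so the target stays at 166 whatever limit is intended. Only the eligible pool changes.

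**Feasibility, intervention stage only**

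Minimum share of the register that must be over 80 if every such patient enrols: 166 / 1500 = 11.07%, more than one in nine.

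With an enrolled fraction c, the required share is 11.07% / c:

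- c = 80%: 13.8%
- c = 70%: 15.8%
- c = 50%: 22.1%

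The actual share over 80 is not in the document. The table treats it as an assumption. Power is Φ(13.5 / (29.7 × √(2/m)) − 1.96), where m is 90% of half the pool. It assumes that everyone eligible enrols (at most 83 per group), that 10% drop out, and that the plan's SD and difference hold in this age group.

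| Assumed share over 80 | Pool (1500 × share) | 166 / pool | Power at best |
|---|---|---|---|
| 2% | 30 | 5.53 | 22% |
| 5% | 75 | 2.21 | 46% |
| 10% | 150 | 1.11 | 75% |
| 15% | 225 | 0.74 | 79% |
| 20% | 300 | 0.55 | 79% |

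A ratio above 1 means that the target cannot be met from the register. At 15% to 20% it can be met if 74% to 55% of those eligible enrol. The residence criterion shrinks each pool by an amount that is not stated.

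**The case against.** The best defence is that eligibility criteria routinely narrow a clinic population, so silence on age in Study setting {9} contradicts nothing. That is right as far as it goes, and the point does not rest on that section alone. The sampling plan's variation in age and employment remains in direct tension with the limit.

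A second defence is that the register's age structure is unknown. That also stands. A reader might infer that the trial cannot recruit, or that almost everyone enrolled would violate the criteria. The document supports neither as a flat statement. Both depend on the share over 80, and choosing a range wholly below 11.07% would simply assume the answer. The feasibility argument also does not reach the interview stage, which has no fixed number and does not draw solely on the clinic.

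A reader might also infer a slip of the keyboard and supply a familiar adult age limit. The document contains no alternative lower limit, and reversing the digits of 80 gives 08, so transposition does not explain it. The intended value cannot be recovered from the text.

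Some supporting arguments are weak and are not used. Physically active days can be counted at any age, and the interview question about work also covers living conditions.

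Finally, this is a journal article, and the full protocol may carry a different figure. That affects how the correction is made. It does not remove the defect, because the article states a value in two places and omits nothing that a fuller document would be expected to supply.

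**Conclusion.** The point holds. The age rule appears in both stages without justification. It conflicts with the maximum-variation plan and is inconsistent with the aim, objectives, study population and background figures. It needs correction or explanation before the eligibility section can be relied on.

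The one feasibility figure that needs no assumption is the 11.07% threshold. Whether 166 over-80s can be found depends on an age distribution that is not given: impossible from this register below the threshold, demanding at 15% to 20%, and harder once residence is applied. The sample-size calculation is unaffected.

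**What to change.** Reconcile the age limit in both parts of Eligibility criteria {10} with Study setting {9} and with the qualitative sampling plan in Sample size {14}.

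- If the figure is an error, correct it in both places to the limit that the sponsor confirms as intended and approved.
- If it is intended, give the rationale, restate the aim, population and sampling plan as concerning over-80s, and report how many registered patients meet the age and residence criteria, so that 166 is shown to be attainable.

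No age value is proposed here.

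The first route costs one figure in two places. If only the article is wrong, a published correction may suffice. If the governing protocol carries the same figure, it needs an amendment. The second route requires rewriting several sections and a count from the clinic register. Neither changes the sample-size calculation.

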### Interventions

#### Explanation for the choice of comparators {6b}

The designed intervention will be carried out only by the intervention group and the control group will only receive routine clinical care. The control group will receive training at the end of the study.

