#### Intervention description {11a}

The intervention will be designed based on HPM constructs for T2D patients. The emphasis of the intervention materials will be on predictors of behavior that have been identified based on the need assessment and a pre-test that will be performed using the researcher-made questionnaire. The first author will recruit participants, will explain the purpose and process of intervention, and will obtain their informed consent to participate. According to the intervention program, the participants will not receive any other relevant education or training during the intervention. Sessions will present by one health education and promotion specialist and one internal specialist medicine, experienced in T2D treatment adherence. Intervention including 10 educational sessions in groups of 15 to 20 patients will be a combination of online and face-to-face methods according to the intervention group conditions. The intervention will be using challenging lectures, educational video clips, posters and pamphlets, and the main content of the sessions will be to promote and improve adherence to treatment in the areas of medication, diet, and physical activity. In-person sessions will be set to an average of 45 min and online sessions to 15 min. The control group will receive training at the end of the study.

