#### Criteria for discontinuing or modifying allocated interventions {11b}

Leaving the study at any time by the participants will not affect the quality of services received in the diabetic clinic. Study participant collected data will be included in the analysis.

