#### Outcomes {12}

The primary outcome is treatment adherence which will be measured according to score of the researcher-made questionnaire and HbA1c test before and 3 months after the intervention. Secondary outcomes include attendance at clinic appointments, weight, healthy diet days, and physically active days.

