#### Methods in analysis to handle protocol non-adherence and any statistical methods to handle missing data {20c}

In case of missing outcome data, the study analyses will be according to available data, relying on an assumption that data is missing at random. Reasons for missingness will be described by a chart, and frequency of miss patients for each stage will be described.

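### Absence from more than two sessions is an exclusion criterion that only randomised intervention patients can meet, so the adherence comparison is expected to favour the programme

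*Protocol article*

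**What the plan says.** All references are to the protocol article.

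- **Eligibility criteria {10}, Intervention stage:** "The exclusion criteria also include participating in intervention sessions (absence of more than two interventional sessions) and not referring to the Diabetes Clinic".
- **Explanation for the choice of comparators {6b}**, on who receives the programme: "The designed intervention will be carried out only by the intervention group and the control group will only receive routine clinical care". It adds: "The control group will receive training at the end of the study".
- **Intervention description {11a}:** "Intervention including 10 educational sessions in groups of 15 to 20 patients". The rule is therefore met by missing three or more of 10.
- **Criteria for discontinuing or modifying allocated interventions {11b}**, next to a sentence about participants who leave: "Study participant collected data will be included in the analysis".
- **Methods to handle non-adherence and missing data {20c}:** "the study analyses will be according to available data, relying on an assumption that data is missing at random".
- **Outcomes {12}:** the primary outcome is treatment adherence, measured by the questionnaire score and HbA1c before and 3 months after the intervention. For the rest: "Secondary outcomes include attendance at clinic appointments, weight, healthy diet days, and physically active days".

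No section says that all randomised participants are analysed in the arm assigned.

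**The concern.** An eligibility criterion should be decidable before randomisation. Absence from sessions is not: it describes behaviour under one of the two allocations. Applied as written, the rule leaves an intervention arm selected for good attendance and an unselected control arm. In a superiority trial whose outcome is adherence, people who miss three or more adherence sessions would plausibly have scored lower whatever the programme did. Their removal raises the intervention mean without any treatment effect. What is at stake is whether a positive result could be attributed to the programme rather than to who was kept in.

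**Working it through.** **1. When, and in whom, the rule operates.** Sequence generation {16a} draws participants from a list of patients whose eligibility is already confirmed. Implementation {16c} assigns them after consent. Sessions follow allocation ({11a}) and are given to one arm only ({6b}). A control cannot be absent from a session during follow-up, so the session rule can remove people from the intervention arm only. This step needs no assumption.

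**2. What the other sections settle.** {11b} retains data already collected. It does not say that a patient excluded under {10} is still invited to the 3-month questionnaire and HbA1c test. {20c} analyses what is available under missing at random. Neither says whether exclusion means from the sessions, from follow-up or from the analysis.

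**3. The plan's own sample size (Sample size {14}).** Inputs: SD 29.7, difference 13.5, two-sided 5%, power 80%.

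n = 2 × (1.960 + 0.842)² × (29.7/13.5)² = 2 × 7.849 × 4.84 = 75.98, so 76 per arm, as stated. Then 76 × 1.10 = 83.6; the plan states 83.

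**4. Size of the bias with an unadjusted t-test.** The documents give neither the excluded fraction f nor the correlation ρ between attendance and final score, so both are assumed. The model has no true effect. Attendance is a standard normal trait, the lowest fraction f of the intervention arm is removed, and all 83 controls are kept.

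- c = Φ⁻¹(f); mean attendance of those retained, m = φ(c)/(1 − f)
- False benefit = ρ × m × 29.7
- Variance factor of retained scores, v = 1 − ρ²(m² − c·m)
- SE = 29.7 × √(v/[83(1 − f)] + 1/83)
- Type I error = P(Z > 1.96 − benefit/SE) + P(Z < −1.96 − benefit/SE)

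For f = 0.20 and ρ = 0.4:

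- c = −0.842 and m = 0.280/0.80 = 0.350.
- False benefit = 0.4 × 0.350 × 29.7 = 4.16 points, which is 31% of 13.5.
- v = 1 − 0.16 × (0.122 + 0.295) = 0.933.
- SE = 29.7 × √(0.933/66.4 + 1/83) = 4.80, and 4.16/4.80 = 0.87.
- Type I error = 13.9%.

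| Excluded | ρ = 0 | ρ = 0.3 | ρ = 0.4 | ρ = 0.5 |
|---|---|---|---|---|
| 10% | 0; 5% | 1.74; 6.6% | 2.32; 7.9% | 2.90; 9.6% |
| 20% | 0; 5% | 3.12; 9.9% | 4.16; 13.9% | 5.20; 19.5% |
| 30% | 0; 5% | 4.43; 14.3% | 5.90; 22.2% | 7.38; 32.6% |

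Each cell gives false benefit in points, then type I error.

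**5. With analysis of covariance, which {20a} also lists.** Suppose attendance correlates 0.4 with the baseline score as well, and baseline and final scores correlate r. Adjustment then leaves roughly (1 − r) of the bias: 4.16 × 0.5 = 2.1 points at r = 0.5, and 4.16 × 0.3 = 1.2 points at r = 0.7. Simulation (20,000 trials per setting, 83 per arm) agrees:

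- 20% excluded: 1.3 to 2.2 points, type I error about 7% to 8% (t-test 14%).
- 30% excluded: type I error about 8% to 11% (t-test about 21% to 22%).

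**6. With no correlation.** There is no bias. Power for 13.5 points falls from 83.4% with 83 per arm to 81.3%, 78.8% and 75.7% at 10%, 20% and 30% excluded.

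**The case against.** **{11b} keeps the data.** It may be meant to, and this softens {10}. A reader might infer that the two sections flatly contradict each other. They do not, because {11b} is written about people who leave and can be read alongside {10}. What stands is that the sections are unreconciled: {11b} neither keeps excluded patients in follow-up nor names an as-randomised analysis.

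**The clinic condition is a baseline criterion.** A reader might infer that patients who stop coming to the clinic are also excluded after randomisation. The article does not establish this. In the abstract, in Study setting {9} and in the qualitative sample section, the same phrase describes who is sampled, and being registered is not the same as currently attending. The condition could also apply to both arms, so the one-arm argument does not rest on it.

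**Analysis of covariance is planned.** This is fair, and it removes a good part of the bias if poor attenders already score lower at baseline. It does not remove all of it, and {20a} does not say which of the listed tests is primary.

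**The drop-out allowance covers it.** A reader might infer that these exclusions come on top of the 10%. {14} does not say what the 10% includes, so that cannot be claimed either way.

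**Reminders will keep the excluded fraction small.** {11c} plans SMS reminders and phone calls after missed sessions. These should help, but no attendance forecast is given.

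**The analysis plan may settle it.** The point is a rule that the protocol states, not a missing detail. An analysis plan cannot recover outcomes that were never collected.

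Read literally, the criterion also excludes people for taking part in sessions. The parenthesis shows this to be a slip of language, and nothing rests on it.

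**Conclusion.** The point holds for the session rule. By the protocol's own wording it acts after randomisation and in one arm only. The direction, towards benefit, is an expectation: it requires that patients who miss sessions would also score worse on adherence, which is likely here but not shown by the text. It would be too strong to say that randomisation is certainly broken, because the article does not say what exclusion entails.

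The size is illustrative. At 20% excluded and a correlation of 0.4, the false benefit is about 4.2 points with type I error near 14% for a t-test. For analysis of covariance it is about 1.3 to 2.2 points with 7% to 8%, given a baseline-final correlation of 0.5 to 0.7. At zero correlation only power is lost. These figures concern the questionnaire score; the documents give no SD for HbA1c, so none is offered there. The clinic condition is ambiguous and needs a clear statement, no more.

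**What to change.** 1. Remove session absence from the exclusion criteria in {10}. Treat missed sessions as non-adherence to the intervention and report attendance descriptively.
2. State that every randomised participant is invited to the 3-month questionnaire and HbA1c test whatever their attendance, using the SMS and phone contact already planned in {11c} and {18b}.
3. Make the analysis of all randomised participants in the arm assigned the primary one, and word {11b} and {20c} to agree with it. Keep any analysis of attenders (per-protocol or complier-average) supplementary.
4. Clarify the condition "absence of more than two interventional sessions) and not referring to the Diabetes Clinic of Shahid Mohammadi Hospital" as regards the clinic. If it is a baseline criterion, say so. If it was meant to apply after randomisation, remove it too, because it selects on something close to the secondary outcome of attendance at clinic appointments.

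The cost is a change of wording, some extra effort to obtain 3-month measurements from poor attenders, and possibly a smaller estimated effect. With all 83 per arm followed and analysed as randomised, this selection bias is zero and power for 13.5 points is 83.4%. The change should be made before recruitment to the intervention stage, since outcomes not collected at 3 months cannot be collected later.
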